# 2. Summary

Cognitive disorders such as deficiencies in executive functions are frequently observed in patients with schizophrenia and are the most significant predictor for restoring or maintaining the ability to work. The treatment of these disorders is therefore of great importance. A promising novel therapeutic option is the neuromodulatory approach of transcranial direct current stimulation. The aim of the proposed study submitted for review is to investigate short-term effects of direct current stimulation on executive function disorders in patients with schizophrenia.

Study design: Multivariate, two-factor mixed-model design with two-tiered between-subject factor *groups* (verum stimulation vs. sham stimulation) and two-tiered within-subject factor *time* intervals (pre vs. post). Patients undergo several neuropsychological procedures before and after the stimulation to assess executive functions.

Patient population: A total of 50 patients with an F2.x diagnosis (i.e. schizophrenia, schizotypal disorder, delusional disorder or schizoaffective disorder) will be randomly assigned to two groups of 25 patients. The proposed study will not involve initiating patient medical drug treatments, nor will the proposed study change any existing medical drug treatments taken (e.g. dose changes). The total time commitment for patients wishing to participate in the study is approx. 60 minutes for inpatients and approx. 3 hours for outpatients.

The study will be conducted in accordance with the provisions of the Professional Code of Conduct for Physicians and in accordance with the current version of the 2013 Helsinki Declaration. Patients will be given written and verbal information before the start of the study and will provide their informed consent in writing. A patient can withdraw their informed consent at any time without providing any justification. Transcranial direct current stimulation is risk free and has few side effects when applied correctly.

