## 6.4 Standardised and normalised neuropsychological test procedures to assess cognitive performance:

All patients will undergo the COGBAT® test set (Aschenbrenner, Kaiser, Pfüller, Roesch-Ely & Weisbrod, 2012) as part of routine clinical diagnostics or during an additional outpatient consultation before beginning the examination. This test set includes a compilation of key neuropsychological parameters to assess the cognitive status of patients with mental disorders. It covers the following parameters: attention, memory, executive functions and processing speed. Specific focus will be placed on performance in the subtests addressing planning ability (“Tower of London”), verbal working memory (“Nback-Verbal“) and response inhibition (“INHIB”). The “SWITCH” test from the Vienna Test System will also be used to assess cognitive flexibility. See Table 1 for an overview of the methods used.

Table 1: Overview of diagnostic, therapeutic and interventional procedures

| **Clinical diagnostics and psychopathology**   - Sociodemographic interview - SCID-I (Wittchen, Zaudig & Fydrich, 1997) - SCID-II - Montgomery-Asberg Depression Rating Scale (MADRS, Montgomery & Asberg, 1979) - Beck Depression Inventory (BDI-II, Hautzinger, Keller & Kühner, 2006) - Personality style and disorder inventory (PSSI, Kuhl & Kazén, 2009) - Inventory of social competence (ISK, Kanning, 2009) - Emotional Competence Questionnaire (EKFS, Rindermann, 2009) - Cognitive performance questionnaire* (FLei, Beblo, Kunz, Lautenbacher, Albert & Aschenbrenner, 2011) |
| --- |
| **Premorbid intelligence**   - MWT-B (Lehrl, 2005) (German multiple choice word selection test) |
| **Neuropsychological diagnostic procedures**  **Vienna test system**  *Information processing speed*   - Trail Making Test Langensteinbach Version*   *Attention*   - Divided attention WAFG test* - Alertness-WAFA test*   *Memory*   - FGT (Figural Memory Test)*   *Executive functions*   - Working memory N-back verbal* - Inhibition-INHIB Go-Nogo* - Cognitive Flexibility Trail Making Test Langensteinbach Version* - Cognitive Flexibility- SWITCH - Convergent Planning-Tower of London-Freiburg Version* |
| **Neurophysiological stimulation**   - DC-Stimulator Mobile, *NeuroConn* |

*Cognitive basic testing from the Vienna Test System (CogBat)

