# 10. Inclusion/exclusion criteria

The inclusion criteria are as follows:

- Patients (age > 18 years) with an F2x diagnosis, i.e. schizophrenia, schizotypal disorder, delusional disorder or schizoaffective disorder in inpatient, day-care or outpatient settings in the Department of Psychiatry and Psychotherapy at the SRH Clinic Karlsbad-Langensteinbach , as well as any persons with the above-mentioned disorders who are not treated in the Department of Psychiatry and Psychotherapy at the SRH Clinic Karlsbad-Langensteinbach but who wish to participate in the study.
- Deficiencies in executive functions (verbal working memory, response inhibition, planning ability, cognitive flexibility).

The exclusion criteria are as follows:

- Impaired intelligence (i.e. IQ ≤ 85)
- Neurological diseases that impact cognition
- Drug use within the last 8 weeks
- Patients that are minors
- Patients of legal age who are unable to give their informed consent

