# 12. Randomisation procedure

In order to ensure effective double-blinding, randomisation is carried out in collaboration with the manufacturer of the direct current device, the Neuroconn company. The company compiles a list of codes, half of which correspond to verum stimulations and the other half to sham stimulations. The sequence of the codes is then scrambled using randomly generated numbers. Before starting each stimulation, one of these codes is entered, upon which either a verum or a sham stimulation is started. This means that neither the investigator nor the patient knows what type of stimulation is being applied.

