# 13. Statistical design

## 13.1 Proposed size of the patient population

The proposed study, will compare mean values (respective average values from the neuropsychological tests) in a two-factor design across independent groups pre-post (2*2 mixed-model design). The statistical hypothesis is as follows:

Statistical hypothesis: There is an interaction between *group*time* in the dependent variable *Performance in the neuropsychological test procedures.*

The size of the patient population required is therefore estimated as a function of the power of the study (1-β), the level of statistical significance (α) and the magnitude of the effect expected (Cohen's d) (Cohen, 1988). The size of the patient population required for the study was estimated using the *G-Power 3* software (Faul, Erdfelder, Lang & Buchner, 2007). To achieve a power of 1-β = 0.9, with a significance level of α = 0.05 and an expected mean effect of d = 0.5, the study needs to enrol n = 23 patients in each group. Assuming a drop-out rate of approximately 10%, the study needs to enrol n = 25 probands in each group. The study will therefore require:

1. 25 patients in the verum stimulation arm
2. 25 patients in the sham stimulation arm

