## 13.2 Statistical analysis

The statistical analysis will be performed on pseudonymised data. Variables of patient characteristics and dependent variables will be analysed using descriptive statistics. For the inferential statistical evaluation of the data, mean value comparisons between the two groups will be performed using pre/post comparisons. Each of the dependent variables will be analysed using on a two-factor mixed-model ANOVA with the between-subject factor group (*verum stimulation* vs. *sham stimulation*) and the within-subject factor time interval (*pre* vs. *post*). Any potential interactions will be further explored by using *a priori* planned comparisons (e.g. t-tests). Where appropriate, several dependent variables will be grouped together to reduce the number of analyses required. If the assumptions for parametric analyses are not satisfied (normal distribution of the error components, homoscedasticity of the error variances, independence of the measured values), the means of individual dependent variables will be compared using a nonparametric test (e.g. Mann-Whitney U-test). If multiple statistical methods are used (t-tests, Mann-Whitney U-tests), the alpha level will be adjusted (Bonferroni correction or Bonferroni Holm procedure) to reflect the overall alpha. The magnitude of individual effects will also be determined (Cohen, 1988) to quantify any potential differences obtained.

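### The group-by-time ANOVA is valid but equals a change-score t-test; adjusting the post score for the pre score is more efficient, by an amount the protocol does not let one fix

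*Protocol*

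**What the plan says.** Section 13.1 describes a comparison of mean test scores "in a two-factor design across independent groups pre-post". It gives the statistical hypothesis as "There is an interaction between" group and time, and sizes the trial on that: 90% power, "with a significance level of α = 0.05", d = 0.5, 23 evaluable and 25 enrolled patients per arm.

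Section 13.2 fixes the model: "Each of the dependent variables will be analysed using on a two-factor mixed-model ANOVA with the between-subject factor group", with time as the within-subject factor. Planned comparisons follow any interaction, and a nonparametric test is the fallback. The document nowhere adjusts the post score for the pre score, and it gives no pre/post correlation.

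Three other passages bear on the point:

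- **Pre scores.** The Summary says "Patients undergo several neuropsychological procedures before and after the stimulation to assess executive functions". The section on neuropsychological test procedures places the baseline test set "as part of routine clinical diagnostics or during an additional outpatient consultation before beginning the examination". SWITCH lies outside that set, so its pre measurement is implied rather than spelled out, but the planned ANOVA needs it just as ANCOVA would.
- **Allocation.** Section 12 provides a scrambled list of codes, "half of which correspond to verum stimulations and the other half to sham stimulations", and a code is entered immediately before each stimulation. The pre score is therefore a genuine pre-treatment covariate.
- **Selection.** Section 10 requires "Deficiencies in executive functions (verbal working memory, response inhibition, planning ability, cognitive flexibility"). It gives no cut-off and does not say whether every domain must be impaired.

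**The concern.** In a two-arm, two-time design the interaction contrast is the between-arm difference in mean change. Testing it subtracts the whole pre score from the post score, whatever the relation between the two. If the regression slope of post on pre is below 1, this adds noise and over-corrects any chance baseline difference between arms. Such differences are not rare with 25 patients per arm.

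ANCOVA estimates the slope instead. Under randomisation both analyses estimate the same treatment effect, and ANCOVA does so with a smaller standard error unless the slope is very close to 1. What is at stake is precision in a trial of 50 patients, from data that are collected anyway. The protocol names the model explicitly, so this is not a detail left open for a later analysis plan.

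**Working it through.** **Inputs.** From 13.1: 23 evaluable per arm, alpha 0.05, power 0.90, d = 0.5. Assumptions: two-sided test; rho 0.3, 0.5 and 0.7; equal pre and post SD (set to 1) before any selection.

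**1. The plan's own figure.** For the interaction, the noncentrality is f² × N × m / (1 − rho). With f = d/2 = 0.25, N = 46, m = 2 and rho = 0.5 it is 0.0625 × 46 × 2 / 0.5 = 11.5. On (1, 44) df the power is 91.2%, and 46 is the smallest even total that reaches 90%. So n = 23 per arm is reproduced. Other correlations give other totals: 62 at rho 0.3 and 28 at rho 0.7.

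**2. Equivalence.** On a simulated data set with 23 per arm, the interaction F and the squared t on change scores were both 10.2410.

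**3. No selection on the pre score.** Var(change) = 2(1 − rho). ANCOVA residual variance = 1 − rho². Their ratio is (1 + rho)/2. Power is for a 0.5 SD between-arm difference; the ANCOVA figure is averaged over chance baseline imbalance and uses 43 df against 44.

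| rho | Var(change) | ANCOVA variance | Ratio | Power, change | Power, ANCOVA |
|---|---|---|---|---|---|
| 0.3 | 1.40 | 0.91 | 0.65 | 29% | 40% |
| 0.5 | 1.00 | 0.75 | 0.75 | 38% | 47% |
| 0.7 | 0.60 | 0.51 | 0.85 | 57% | 63% |

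Simulation at rho 0.5 (10,000 runs) gave 38.3% and 47.8%. Under no effect the rejection rates were 5.2% and 5.4%.

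**4. All patients below -1 SD on the test analysed.** The cut-off is assumed, and rho refers to the unselected population. Truncating a standard normal below -1 leaves variance 1 + 1.525 − 1.525² = 0.199. The slope stays at rho, so Var(change) = (1 − rho)² × 0.199 + (1 − rho²), and the ANCOVA variance is unchanged.

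| rho | Var(change) | ANCOVA variance | Ratio | Power, change | Power, ANCOVA |
|---|---|---|---|---|---|
| 0.3 | 1.008 | 0.91 | 0.90 | 38% | 40–41% |
| 0.5 | 0.800 | 0.75 | 0.94 | 46% | 47% |
| 0.7 | 0.528 | 0.51 | 0.97 | 63% | 63% |

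**5. At the setting that reproduces n = 23.** For the change score the noncentrality is (n/2) × D² / [2(1 − rho)] = 11.5 × D² at rho 0.5. A value of 11.5 therefore means D = 1.0 SD. Without selection, ANCOVA raises power from 91% to about 97%, or reaches 90% with 18 per arm instead of 23.

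**6. Possible loss.** With change-score power held at 91.2%, ANCOVA falls behind only above rho of about 0.955, and by less than half a point (90.9% at rho 0.98).

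**The case against.** The strongest reply is that sections 13.1 and 13.2 agree with each other, the planned test holds its type I error, and choosing between two valid analyses is a matter of taste. The first two parts stand. The third does not: the covariate is already collected, precedes allocation and costs one degree of freedom.

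A second objection concerns size. The larger gains assume no selection on the pre score, while section 10 selects on executive deficit. This stands and belongs with the main result. One might suppose that selection favours ANCOVA because it lowers the observed correlation. With direct selection on the analysed score the reverse holds: ANCOVA's advantage is (1 − slope)² × Var(pre), and selection shrinks Var(pre) while leaving the slope alone. How far this applies to each test is open, because section 10 gives neither a cut-off nor a rule on how many domains must be impaired.

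A reader might also infer that the correlation must be well below 1, since the two scores come from separate consultations. The protocol gives neither a retest reliability nor an interval between visits, so this is an assumption.

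Finally, the starting powers of 29% to 57% read d = 0.5 as a 0.5 SD difference between arms. On the reading that reproduces n = 23, the planned test already meets its 90% target.

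**Conclusion.** The point holds as one of efficiency. The planned analysis is a change-score test and is less precise than baseline adjustment for any correlation up to about 0.95. At 23 per arm and a 0.5 SD difference, the gain lies between about 12, 9 to 10 and 6 points of power (rho 0.3, 0.5, 0.7; no selection) and roughly 3, 1 and at most 1 points (everyone below -1 SD). The range rests on an unstated correlation, an unstated entry cut-off and equal pre and post variances before selection.

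Two stronger readings are not supported. The planned ANOVA is neither biased nor invalid: over-correction of a chance imbalance affects the individual result but averages out under randomisation. Nor does ANCOVA rescue the sample size: if d = 0.5 means a 0.5 SD difference and rho is 0.5, 90% power needs 86 per arm with change scores and still 65 with ANCOVA (no selection).

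**What to change.** - **Section 13.2:** make the primary analysis ANCOVA, with the post score regressed on arm and the pre score of the same test (or composite). Report the adjusted between-arm difference with its 95% CI. Keep the mixed ANOVA as a supporting analysis.
- **Section 13.1:** restate the hypothesis as a baseline-adjusted difference between arms, and state the pre/post correlation assumed for the sample size.
- **Consequential wording in 13.2:** the planned comparisons now depend on an interaction, and the nonparametric fallback does not say which score it uses. Align both with the new primary analysis.

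The cost is a few sentences across two sections and one residual degree of freedom. No new data, visits or patients are needed. Settle the change before unblinding, so that the choice of analysis cannot follow the results.

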# 5. Primary and secondary endpoints

The primary endpoint for the aforementioned hypotheses is the improvement of cognitive performance in the area of executive functions in patients with schizophrenia, measured using several standardised neuropsychological testing procedures. There are no other secondary objectives.

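### The alpha correction does not expressly cover the primary group-by-time tests, and the stated power holds only for a single test at 0.05

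*Protocol*

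**What the plan says.** Protocol Section 5 defines one primary endpoint, improvement in executive function, "measured using several standardised neuropsychological testing procedures". It names no leading variable and says there are no secondary objectives. Section 6.5 lists four tests given at the stimulation visit: Tower of London, N-back verbal, INHIB and SWITCH. The number of scores taken from each is not given.

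Section 13.1 states one hypothesis, a group-by-time interaction in one dependent variable (test performance), and refers to "respective average values from the neuropsychological tests". It sizes the trial "with a significance level of α = 0.05" with "an expected mean effect of d = 0.5" and a power of 0.9, which gives 23 patients per group, raised to 25 for drop-out.

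Section 13.2 then says: "Each of the dependent variables will be analysed using on a two-factor mixed-model ANOVA". Grouping is optional: "Where appropriate, several dependent variables will be grouped together to reduce the number of analyses required". The multiplicity rule is: "If multiple statistical methods are used (t-tests, Mann-Whitney U-tests), the alpha level will be adjusted (Bonferroni correction or Bonferroni Holm procedure"; its stated aim is to respect the overall alpha. In the same section, t-tests are an example of how an interaction is followed up, and the Mann-Whitney test is the replacement when parametric assumptions fail.

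**The concern.** The group-by-time interactions carry the trial's only hypothesis, and there may be four or more of them. The sentence that controls alpha is triggered by the use of several statistical methods, not by the number of outcomes, and its examples leave out the ANOVA. Read literally, the follow-up t-tests and the nonparametric fallback are corrected while the main parametric tests are not. No section says how many interactions must be significant to support the hypothesis in Section 4, so one significant result out of four could be reported as improved executive function.

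The sample size was derived for one test at 0.05. Whichever way the correction is read, one stated property is therefore in doubt: overall alpha on the literal reading, 90% power for each test on the generous one.

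**Working it through.** **Inputs.** From Section 13.1: alpha 0.05, power 0.90, d = 0.5, 23 per group (46 in total). From Section 6.5: four tests. From Section 13.2: one 2 x 2 mixed ANOVA per dependent variable. Assumed, because the Protocol does not give them: f = d/2 = 0.25, pre-post correlation 0.5, an F test (two-sided in effect), and a between-test correlation of change scores from 0 to 0.8.

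**Step 1: reproduce the sample size.** For the interaction with two groups and two time points, the noncentrality is f² x N x m / (1 - rho) = 0.0625 x 46 x 2 / 0.5 = 11.5, with 1 and 44 degrees of freedom. Power at alpha 0.05 is 0.912, and 46 is the smallest even total that reaches 0.90. The stated 23 per group is therefore reproduced for one test at 0.05. Other inputs miss it:
- Pre-post correlation 0, 0.3 or 0.7 gives totals of 88, 62 or 28.
- A plain two-group comparison at d = 0.5 gives 85 per group two-sided, or 69 one-sided.

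**Step 2: the literal reading, four interactions each at 0.05.** If the tests are independent, the chance of at least one false positive is 1 - 0.95^4 = 0.185. For correlated tests, the interaction F test is equivalent to a two-sample t-test on change scores. Four equicorrelated t-tests with 23 per group were simulated (200,000 runs per value):

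| Between-test correlation | Familywise error |
|---|---|
| 0.2 | 18.0% |
| 0.3 | 17.5% |
| 0.4 | 16.7% |
| 0.5 | 15.6% |
| 0.6 | 14.5% |
| 0.7 | 13.1% |
| 0.8 | 11.4% |

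The range is thus about 11-19%, or 2.3 times (11.4/5) to 3.7 times (18.5/5) the nominal 5%.

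**Step 3: a different number of tests (independent).** If grouping leaves fewer tests: three give 1 - 0.95^3 = 14.3%, two give 9.8%, one gives 5%. If more variables are tested: six give 26.5% and eight give 33.7%.

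**Step 4: the generous reading, correction applied to the four interactions.** The Bonferroni level, which is also the first Holm step, is 0.05/4 = 0.0125. Familywise error is then at most 0.05 (1 - 0.9875^4 = 0.049 if independent). With the Step 1 inputs and 46 patients, per-test power falls from 0.912 to 0.780. Keeping 90% per test at 0.0125 would need 62 evaluable patients, 31 per group.

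**The case against.** The strongest reply is that the plan already commits to controlling overall alpha, and that the parenthesis merely gives loosely worded examples of repeated testing. The Mann-Whitney test supports this reading: it is not a follow-up but a replacement that compares individual outcomes, so the rule does reach outcome-level comparisons in that branch. This stands, and it makes the defect one of unclear coverage rather than deliberate exclusion. It does not remove the defect, because the tests that carry the hypothesis still go unnamed.

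A reader might infer that each ANOVA will be tested at 0.05. The Protocol does not say so: 0.05 appears only in the sample-size section. Nor is 16% a floor for the error rate. Optional grouping, or a correlation above about 0.5, brings it lower, and the correlation is unknown. A reader might also infer that grouping will be chosen after seeing the data. The Protocol does not say when it is decided, and a statistical analysis plan may settle both grouping and the score for each test.

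On power, Holm holds only the smallest p-value to 0.0125, so 78% is a lower limit for each test. If all four tests respond as assumed, the chance that at least one is significant is at least that high. This also stands. But Section 13.1 does not say that its 90% means success on any one test, and if only one test responds, that test must in general pass at or near 0.0125.

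Finally, the averaged values mentioned in Section 13.1 could hint at a composite. None is defined, and Section 13.2 analyses each variable separately.

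**Conclusion.** The point holds as a gap in coverage and a mismatch between Sections 13.1 and 13.2. The Bonferroni/Holm rule does not expressly apply to the primary group-by-time tests. Four unadjusted tests at 0.05 would give a familywise error of about 11-19%. That figure is conditional on exactly four tests, no adjustment, and a between-test correlation between 0.8 and 0.

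If the rule does cover the ANOVAs, the 90% power is not delivered for each test: it is about 78% at the first step, given f = 0.25 and a pre-post correlation of 0.5. It does not follow that the sample size is wrong outright, since that depends on what counts as success, which the Protocol leaves unstated. What d = 0.5 is meant to measure is a separate question, and this conclusion does not rest on it beyond the conversion stated above.

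**What to change.** In Section 13.2, state that the Holm procedure applies across the primary group-by-time tests and across any nonparametric tests that replace them. Before unblinding, fix one score per test and any grouping of variables. In Section 13.1, restate the per-test power at alpha 0.0125, about 78% under the assumptions above, without enrolling more patients.

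This changes wording only. The price is lower per-test power than the Protocol now claims.

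An acceptable alternative, at the sponsor's choice, is a single pre-specified composite of the four tests, tested once at 0.05. That matches the single-test basis of Section 13.1. Its drawback is that it dilutes an effect limited to one test, a real possibility here because Section 3.3.2 describes earlier benefit mainly in verbal working memory.

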## 6.5 Experimental procedure and time demands on the patients

Following the standard routine diagnostics for inpatients or the first consultation for outpatients (see above), patients will be invited to attend a second consultation. At the beginning of the examination, patients will initially be given a brief explanation about the *DC-Stimulator Mobile*, before application of the device. The device will then be started and the patients asked to complete the “Tower of London”, “N-back verbal”, “Inhib” and “Switch” tests from Schuhfried's Vienna Test System. The selection of test procedures is based on the concept of Miyake's executive functions described above (2000). Since the duration of the tDCS stimulation is shorter than the total time required for the procedures, the stimulation is switched off during the course of the examination. The procedure is finished when test procedures have been completed. The total time required to participate in the study beyond the routine diagnostics is approximately 60 minutes for in-patients. This includes both tDCS stimulation and the processing of neuropsychological procedures. The time required for outpatients is approximately 2 hours for the first consultation and approximately 1 hour for the second consultation, i.e. a total of 3 hours for the entire study period.

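### Section 13.2 allows plain Bonferroni as an alternative to Holm, although Holm holds the same overall alpha and never rejects less: a minor, free gain in power

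*Protocol*

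**What the plan says.** Protocol section 13.2 makes the adjustment conditional: "If multiple statistical methods are used (t-tests, Mann-Whitney U-tests") then "the alpha level will be adjusted (Bonferroni correction or Bonferroni Holm procedure) to reflect the overall alpha". It gives no rule for choosing between the two corrections, and it does not say how many tests are in the family.

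The number of tests is only partly visible. Section 6.5 has patients "complete the “Tower of London”, “N-back verbal”, “Inhib” and “Switch” tests" at the stimulation session, which suggests at least four outcomes. Section 13.2 then states: "Each of the dependent variables will be analysed using on a two-factor mixed-model ANOVA". It also allows the count to shrink: "Where appropriate, several dependent variables will be grouped together to reduce the number of analyses required". No simultaneous confidence intervals are planned; effect sizes are.

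The sample size in section 13.1 is 23 evaluable patients per group for d = 0.5: "To achieve a power of 1-β = 0.9", "with a significance level of α = 0.05".

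**The concern.** The text treats the two corrections as interchangeable, and for hypothesis decisions they are not. Bonferroni compares every p-value with alpha/m. Holm orders the p-values and compares them in turn with alpha/m, alpha/(m-1), and so on up to alpha, stopping at the first failure. Both control the family-wise error rate whatever the dependence between tests. No Holm threshold is below alpha/m, so Holm rejects every hypothesis that Bonferroni rejects.

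Plain Bonferroni is thus a dominated option that the plan expressly permits. What is at stake is the answer for individual domains. If stimulation improves more than one of working memory, inhibition, planning and flexibility, Bonferroni can miss a domain effect that Holm would confirm at the same overall error rate. The usual reason to keep Bonferroni, simple simultaneous intervals, is not used in this plan.

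**Working it through.** **Inputs.** From section 13.1: 23 evaluable per group, alpha 0.05, power 0.90, d = 0.5, group-by-time interaction. Assumed, because the protocol gives no figure: pre-post correlation rho = 0.5, a family of m = 4 tests, two-sided testing, and correlation between tests from 0 to 0.6.

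**1. Reproduce the stated sample size.** For the interaction in a 2 x 2 mixed ANOVA with f = d/2 = 0.25, the noncentrality is lambda = N x 2 x f²/(1 - rho).
- N = 46: 46 x 2 x 0.0625/0.5 = 11.5; power 0.912.
- N = 44: 44 x 2 x 0.0625/0.5 = 11.0; power 0.8997, just short of 0.90.

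So 23 per group is reproduced under rho = 0.5. The square root of 11.5 is 3.39, which equals 1.0 x sqrt(23/2). On the change-score scale, the effect that reproduces the stated size is therefore a difference of 1.0 SD of change.

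**2. Thresholds for four tests.**
- Bonferroni: 0.05/4 = 0.0125 for every test.
- Holm: 0.0125, 0.0167, 0.025, 0.05 in order.

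Power of one test at 1.0 SD with 23 per group is 0.780 at 0.0125, 0.812 at 0.0167, 0.854 at 0.025 and 0.912 at 0.05. The first threshold is the same for both rules, so the chance of at least one rejection must be identical.

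**3. Simulation, 100,000 runs per scenario, 23 per group.** Average power per true effect (%), Bonferroni against Holm:

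| Responding domains | Correlation 0 | 0.3 | 0.5 |
|---|---|---|---|
| One of four, 1.0 SD | 78.3 / 78.4 | 78.0 / 78.1 | 77.8 / 77.9 |
| Two of four, 1.0 SD | 78.0 / 80.7 | 78.2 / 80.6 | 78.1 / 80.3 |
| Four of four, 1.0 SD | 78.0 / 88.5 | 78.0 / 87.4 | 78.0 / 86.6 |
| Four of four, 0.5 SD | 19.5 / 21.9 | 19.5 / 22.8 | 19.4 / 23.4 |

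Extending the correlation to 0.6 gives a range of 86 to 89% for Holm with four of four at 1.0 SD, a gain of 8 to 11 points. A separate run (60,000 replicates, correlation 0 to 0.6) for two of four at 0.5 SD gives 19% against 20 to 21%.

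The chance of confirming all four domains at 1.0 SD is 37, 46 and 51% with Bonferroni and 68, 72 and 75% with Holm, at correlations 0, 0.3 and 0.5.

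**4. Hand check of the one-domain case.** Holm adds a rejection when the true effect's p-value lies between 0.0125 and 0.0167 and some null test falls below 0.0125. The chance of the latter with three independent nulls is 1 - 0.9875³ = 0.037. The gain is about (0.812 - 0.780) x 0.037 = 0.001, as simulated.

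**5. Error control.** In every run Holm rejected everything Bonferroni rejected. Family-wise error was at most 0.049 for either rule.

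**The case against.** The strongest reply is that nothing here is wrong. The plan commits to adjusting, names two valid procedures, and one of them is Holm. A statistical analysis plan that is not shown may fix the choice. This bears on the weight of the point but does not remove it: the protocol is not silent, it authorises the weaker rule.

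Three further objections stand and limit the size.

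- **The family.** The clause names t-tests and Mann-Whitney U-tests. The simulated change-score tests are equivalent to the group-by-time interactions, which section 13.2 assigns to the ANOVA and does not name in the adjustment. Read literally, the figures illustrate how the two rules differ; they do not measure the power of tests the plan certainly adjusts.
- **The best case.** The 8 to 11 points need all four domains to respond at 1.0 SD. Section 3.3.2 reports earlier benefit on verbal working memory and none shown for planning or response inhibition. One or two responding domains are therefore at least as well supported by the protocol's own background, and there the gain is 0 to 3 points.
- **Grouping.** With two composites both responding at 1.0 SD, the comparison is 85% against 89 to 90%, a gain of 4 to 5 points.

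A reader might infer more than the text supports. The open choice does not threaten type I error: Bonferroni's rejections are a subset of Holm's, so even picking between them after seeing the data cannot exceed Holm's error level. Nor does naming Bonferroni first show that it is preferred; the text gives no order of preference.

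**Conclusion.** The point holds as a low-severity efficiency matter. Section 13.2 permits a rule that is never better than its named alternative for deciding which hypotheses to reject, and nothing in the plan gives a reason to keep it. Any loss arises only if the analyst picks Bonferroni and more than one effect is real.

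Its size ranges from about nil to 11 points of average power per true effect, depending on how many domains respond and how strongly. That range rests on an assumed family of four, 23 evaluable patients per arm, effects of 0.5 or 1.0 SD of change, and correlations between tests of 0 to 0.6. A reader might take the upper end as the power this trial stands to lose; the documents do not support that, because they fix neither the family nor the number of responding domains. The conclusion that Holm is at least as good does not depend on any of these assumptions.

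**What to change.** In section 13.2, strike the plain Bonferroni option and state that the Holm step-down procedure is used wherever the plan adjusts alpha.

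This changes one line. It needs no new data or patients, leaves the overall error control as it is, and removes one open analyst choice. The only drawback is that simultaneous confidence intervals matching Holm are less simple than Bonferroni intervals. The plan does not call for simultaneous intervals, and ordinary 95% intervals can be reported beside the Holm decisions.
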